### Assessment of intervention fidelity

We will contact different practices in each of the four study arms over regular intervals to check whether practices are receiving their randomly allocated messages, and that the messages are continuing over the intervention period as planned.

### Sample size

The sample size calculations, based on methods described by Donner *et al*. [12], were undertaken using a programme developed by Campbell *et al*. [13]. They were originally based upon the following assumptions: The study would be carried out in a population of 39 practices with an average number of 62 patients per practice (patients with diabetes whose care is undertaken either by the general practice or shared between the general practice and hospital); a significance level of 5%; 80% power; for binary outcomes (*e.g*., was a test ordered?) the intraclass correlation coefficient (ICC) equals 0.2; and for continuous outcomes (*e.g*., mean HbA1c) the ICC = 0.05.

Under these assumptions, we will be able to detect a 20% improvement (from 55% to 75%) in a binary outcome measure and an effect size of 0.24 in a continuous outcome measure. This represents a change of 0.35% in mean HbA1c, 0.26 mmol/L in mean cholesterol, 4.78 mmHg in mean systolic blood pressure and 2.45 mmHg in mean diastolic blood pressure. These were based on estimated standard deviations of 1.45, 1.07, 19.9 and 10.2, respectively, from a recent trial of a diabetes recall and management system for primary care [14].

When we subsequently extended the evaluation, we kept the same basic assumptions for the power calculation, with the exception that the number of participating practices had fallen to 34. We will be able to detect a 21% improvement (from 55% to 76%) in a binary outcome measure and an effect size of 0.25 in a continuous outcome measure. This represents a change of 0.36% in mean HbA1c, 0.27 mmol/L in mean cholesterol, 4.98 mmHg in mean systolic blood pressure and 2.55 mmHg in mean diastolic blood pressure.

The statistical power for the evaluation of the foot examination message is problematic. Our original assumptions during the planning of Phase Two had been based on pre-intervention compliance much lower than the 90% suggested by recently available QOF data. Based on the preceding assumptions (including 34 practices), we have only 58% power to detect a 5% improvement (from 90% to 95%).

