### Statistical analysis

For Phase One, the dependent variables will be the last recorded HbA1c and cholesterol levels. For Phase Two, the dependent variables will be the last recorded levels of diastolic and systolic BP and the proportions of patients with recorded foot inspections.

Subjects included in the analysis will be all those patients registered with each practice with a diagnosis of diabetes whose care is undertaken either by the general practice or shared between the general practice and hospital. Where multiple observations (*e.g*., of cholesterol levels) are available for one subject within a pre- or post-intervention period, we will use the most recent observation. Data will be analysed using multilevel modelling with patients nested within practices. Within practices, a binomial error structure will be assumed for binary variables and a normal error structure for continuous variables. In each case, variation between practices will be fitted as a random effect with a Gaussian distribution.

The dependent variable will be the outcome measure corresponding to the period after the intervention. Where appropriate, the pre-intervention value of the variable will be included in the model as a covariate. The difference between practices receiving a particular intervention and those not receiving that intervention will be included as a fixed effect.

We will assess any change in blood pressure across all participants but fit a different effect for patients with microalbuminuria at baseline. This analysis will allow us to determine whether the messages had a differential effect according to whether microalbuminuria is present.

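### The stated 58% power for the foot-inspection message contradicts the plan's own binary ICC of 0.2, which gives about 22%; 58% matches the ICC of 0.05 set for continuous outcomes

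*Protocol article*

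**What the plan says.** The Sample size section of the protocol article sets its inputs once. The population is "39 practices with an average number of 62 patients per practice", with "a significance level of 5%; 80% power". For binary outcomes "the intraclass correlation coefficient (ICC) equals 0.2"; by contrast, "for continuous outcomes (*e.g*., mean HbA1c) the ICC = 0.05". For the extended evaluation the section keeps these assumptions, except that "the number of participating practices had fallen to 34". On that basis it says "We will be able to detect a 21% improvement (from 55% to 76%) in a binary outcome measure" and gives an effect size of 0.25 for continuous outcomes.

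The last paragraph turns to foot examination. It calls the power problematic because recent QOF data put baseline compliance at 90%, and then states: "Based on the preceding assumptions (including 34 practices), we have only 58% power to detect a 5% improvement (from 90% to 95" per cent. It gives no separate ICC for this outcome.

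The Outcomes section makes foot inspection a Phase Two primary outcome. The Statistical analysis section takes as its dependent variable "the proportions of patients with recorded foot inspections" and gives binary variables a binomial error structure.

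**The concern.** The sentence claims to rest on the assumptions already listed, and for a binary outcome those include an ICC of 0.2. With 62 patients per practice that ICC inflates the variance about thirteenfold. A five-point difference near 90% would then be very hard to detect with 34 practices, and 58% looked too high.

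Foot inspection is the only binary primary outcome among the four trials. Power of 58% suggests a better-than-even chance of finding the target improvement. Power of 22% means that a true five-point gain would be missed nearly four times in five. A reader who relies on the printed figure would give a non-significant result more weight than it can bear.

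**Working it through.** **Inputs.** From the Sample size section: 34 practices, 62 patients per practice, 5% significance, ICC 0.2 (binary) and 0.05 (continuous), 90% versus 95%. Two inputs are assumed because the article does not state them: a two-sided test and 17 practices per arm. Each message is compared with its control across all practices, so n per arm = 17 × 62 = 1,054.

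**Formulas.**
- Design effect DE = 1 + (62 − 1) × ICC
- Effective n per arm = 1,054 / DE
- SE = √[(p₁(1 − p₁) + p₂(1 − p₂)) / effective n]
- Power = Φ(|p₂ − p₁| / SE − 1.96)

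This is the unpooled form. The pooled form uses the average proportion for the null variance and differs only slightly.

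**Step 1: check the method on the section's other figures.**
- 55% to 76%, 34 practices, ICC 0.2: DE = 13.2; effective n = 79.8; SE = √[(0.2475 + 0.1824) / 79.8] = 0.0734; 0.21 / 0.0734 = 2.86; power = Φ(0.90) = 81.6% (pooled 80.3%). The stated power is 80%. With ICC 0.05 the same comparison would have 99.9% power, so this figure was computed with 0.2.
- 55% to 75%, 39 practices, ICC 0.2: power is 81.5% (pooled). The stated power is 80%.
- Continuous outcome, 34 practices, ICC 0.05: DE = 4.05; effective n = 260.2; detectable effect size = (1.96 + 0.84) × √(2 / 260.2) = 0.246. The stated value is 0.25.

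**Step 2: foot inspection, 90% to 95%.** The variance sum is 0.90 × 0.10 + 0.95 × 0.05 = 0.09 + 0.0475 = 0.1375.

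| | ICC 0.2 (plan's binary value) | ICC 0.05 (plan's continuous value) |
|---|---|---|
| Design effect | 13.2 | 4.05 |
| Effective n per arm | 79.8 | 260.2 |
| SE | 0.0415 | 0.0230 |
| 0.05 / SE | 1.205 | 2.175 |
| Power, unpooled | 22.5% | 58.5% |
| Power, pooled | 22.2% | 58.2% |
| Power, t with 32 df | 21.4% | 56.0% |

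Solving the pooled formula for the ICC that gives exactly 58% yields 0.0503.

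**Step 3: look for another route to 58% at ICC 0.2** (pooled form).

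| Variation | Power |
|---|---|
| One-sided test | 32.7% |
| 18/16 split of practices | 21.5% |
| 39 practices instead of 34 | 24.9% |
| 34 practices in each arm | 39.6% |
| Unlimited patients per practice (effective n = 17 / 0.2 = 85) | 23.4% |

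None comes near 58%.

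**Step 4: what ICC 0.2 implies.** From a 90% baseline, 80% power needs about 99.7% in the intervention arm (pooled form), which is almost the ceiling. The 95% confidence half-width is about 1.96 × 0.0415 = 0.081, or 8 percentage points, against a target of 5.

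**The case against.** The arithmetic is hard to dispute, but several qualifications can be raised.

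- **Cause.** The article does not say which ICC produced the 58%. The authors may have chosen a lower ICC deliberately at a 90% baseline and not said so. This stands: the carry-over of 0.05 is inferred from a near-exact match. It does not rescue the sentence, because a separate ICC is not among the assumptions it invokes.
- **Sidedness.** The article does not state it, and a one-sided test with an ICC of about 0.075 would also give 58%. That ICC appears nowhere in the plan, and a one-sided test would give 88% rather than 80% for 55% to 76%.
- **Baseline adjustment.** The analysis may include the pre-intervention value as a covariate, which could raise real power. So 22% is the power under the stated design inputs and does not forecast the power of the fitted model. Adjustment is not a stated power assumption, and the other figures reproduce without it.
- **Disclosure.** The article already calls the power problematic and puts it below 80%. This is fair: the error changes the depth of the shortfall and not whether one is admitted. The gap between 58% and 22% is still material to how a null result is read.
- **Consequences.** No section ties the choice of foot inspection as a primary outcome to the 58%, and correcting it alters neither the design nor the analysis model. This also stands.

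**Conclusion.** The point holds. Under the assumptions that the sentence cites, power to detect a rise from 90% to 95% is about 22%, so the stated 58% is too high by about 36 percentage points (58 − 22). It matches the plan's continuous-outcome ICC of 0.05 and contradicts its binary ICC of 0.2. The result assumes equal arms and a two-sided test, and relaxing either does not change the conclusion. Which ICC the authors intended for foot inspection cannot be settled from the article. The sentence as written is wrong in either case: the figure is wrong if 0.2 applies, and the stated basis is wrong if 0.05 was meant.

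**What to change.** Revise the last paragraph of the Sample size section in one of two ways:

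1. If the binary ICC of 0.2 applies, replace 58% with about 22%. State that, from a 90% baseline, 80% power would need a rise to more than 99%.
2. If 0.05 was intended for foot inspection, state it as a separate assumption, justify it, and show both values: about 22% at ICC 0.2 and 58% at ICC 0.05.

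In either case, state whether the test is two-sided. It would also help to say in advance that this comparison will be read from its estimate and confidence interval, and that a non-significant result is not evidence of no effect. This is advice on reporting and does not follow from the arithmetic alone.

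The cost is one rewritten paragraph and, under the first option, a less favourable stated power. No extra practices, data or changes to the analysis model are needed.

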### Statistical analysis

For Phase One, the dependent variables will be the last recorded HbA1c and cholesterol levels. For Phase Two, the dependent variables will be the last recorded levels of diastolic and systolic BP and the proportions of patients with recorded foot inspections.

Subjects included in the analysis will be all those patients registered with each practice with a diagnosis of diabetes whose care is undertaken either by the general practice or shared between the general practice and hospital. Where multiple observations (*e.g*., of cholesterol levels) are available for one subject within a pre- or post-intervention period, we will use the most recent observation. Data will be analysed using multilevel modelling with patients nested within practices. Within practices, a binomial error structure will be assumed for binary variables and a normal error structure for continuous variables. In each case, variation between practices will be fitted as a random effect with a Gaussian distribution.

The dependent variable will be the outcome measure corresponding to the period after the intervention. Where appropriate, the pre-intervention value of the variable will be included in the model as a covariate. The difference between practices receiving a particular intervention and those not receiving that intervention will be included as a fixed effect.

We will assess any change in blood pressure across all participants but fit a different effect for patients with microalbuminuria at baseline. This analysis will allow us to determine whether the messages had a differential effect according to whether microalbuminuria is present.

The revised study can be conceptualised as four separate trials of different education messages with each message being targeted at a specific outcome. The first step in the analysis will be to obtain estimates of the effect of each intervention on the primary outcome with which it is associated. The second step will be to estimate the effect of each intervention on the secondary outcomes with which it is associated. The final step will be to investigate whether an intervention has had a secondary effect on outcomes other than those targeted. The interventions have been introduced two at a time; allocation of practices to interventions within each pair was according to a two-by-two factorial design. Estimates of the secondary effects of an intervention will be based on a main effects model that also includes the effect of the intervention (introduced at the same time) which targets that particular outcome.

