### Design

This programme comprises four cluster randomised controlled trials (one for each of the four interventions) with general practices as the unit of randomisation. It is important that the study uses a randomised design because there will inevitably be other initiatives relating to diabetes that will occur during the time of the study. It is only by using a randomised design that any observed effects can be confidently attributed to the interventions.

The availability of practice-level data used to measure performance for the Quality Outcomes Framework (QOF) allowed us to stratify randomisation. For Phase One, stratification was according to both the number of diabetic patients per practice and the QOF score (proportion of diabetic patients achieving HbA1c of 7.4 or less). For Phase Two, stratification was according to both the proportion of patients with a record of foot examination and the proportion of patients with a record or blood pressure of 145/85 or less. Therefore, practices, stratified by performance, were randomly allocated to each intervention independently. Randomisations were conducted independently by a statistician using numbers randomly generated by computer.

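### The test for a different blood-pressure message effect in microalbuminuria has no practice-level random coefficient as written, so its interval is too narrow if the microalbuminuria gap varies between practices

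*Protocol article*

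**What the plan says.** The Design section describes cluster randomised trials "with general practices as the unit of randomisation". The Statistical analysis section sets out one model for all outcomes:

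- Levels: "Data will be analysed using multilevel modelling with patients nested within practices".
- Between-practice variation: "In each case, variation between practices will be fitted as a random effect with a Gaussian distribution".
- Message: "The difference between practices receiving a particular intervention and those not receiving that intervention will be included as a fixed effect".
- Baseline: the pre-intervention value enters as a covariate where appropriate.

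For blood pressure it adds: "We will assess any change in blood pressure across all participants but fit a different effect for patients with microalbuminuria at baseline". The stated purpose is inferential: "This analysis will allow us to determine whether the messages had a differential effect according to whether microalbuminuria is present".

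No random coefficient for microalbuminuria is mentioned, and none is expressly ruled out. The Sample size section gives an ICC of 0.05 for continuous outcomes, 62 patients per practice, SDs of 19.9 and 10.2 mmHg for systolic and diastolic pressure, and the power for the extended evaluation "with the exception that the number of participating practices had fallen to 34". It gives no figure for the differential effect.

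**The concern.** Call the difference in mean blood pressure between patients with and without microalbuminuria in one practice that practice's gap. The differential effect asks whether gaps differ between message and control practices. Its error has two parts: patient-level noise within each gap, and real variation in the gap between practices for reasons unrelated to the message.

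A random intercept removes what is common to all patients of a practice. It leaves no room for the second part, because it treats the gap as identical in every practice of an arm. Any real variation is then averaged over 34 × 62 = 2,108 patients instead of 34 randomised practices. The protocol allows for clustering in the overall comparison; followed as written, it does not do so in this one.

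This matters because the blood-pressure message itself depends on the albumin:creatinine ratio (Table 1), and blood-pressure control by microalbuminuria status is a secondary outcome. A claim that the message works differently in the two groups would be a main reading of this trial, and chance differences between practices could produce it more often than the nominal 5%.

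**Working it through.** **The plan's own figure.** Design effect 1 + 61 × 0.05 = 4.05. Patients per arm 17 × 62 = 1,054 (equal arms assumed). Detectable effect (1.96 + 0.84) × √(2 × 4.05/1,054) = 0.246, rounding to the stated 0.25. Then 0.25 × 19.9 = 4.98 and 0.25 × 10.2 = 2.55 mmHg, as stated. These inputs are therefore the plan's, and they are used below for systolic pressure.

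**Inputs from the protocol.** Total variance 19.9² = 396.0. Between-practice variance 0.05 × 396.0 = 19.8 (SD 4.45 mmHg). Within-practice variance σ² = 0.95 × 396.0 = 376.2.

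**Assumptions, because the documents give no figure.**
- Prevalence p of microalbuminuria: 10%, 20% or 30%.
- Correlation r between a practice's effects in the two patient groups: 0.9, 0.8 or 0.5. The gap variance is τ² = 2 × 19.8 × (1 − r) = 3.96, 7.92 or 19.8, so the gap SD is 2.0, 2.8 or 4.45 mmHg.

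**Formulas.**
- Variance of one practice's gap under the random-intercept model: v = σ² × [1/(62p) + 1/(62(1 − p))].
- True variance: v + τ².
- SE of the differential effect: √(4 × variance/34).
- True type I error of the nominal 5% test: P(|Z| > 1.96 × √(v/(v + τ²))).

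**Worked case (p = 20%, r = 0.5).** v = 376.2 × (1/12.4 + 1/49.6) = 37.9. Model SE = √(4 × 37.9/34) = 2.11 mmHg. True SE = √(4 × 57.7/34) = 2.61 mmHg. Type I error 11.2%.

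**Without baseline pressure in the model.**

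| Gap SD (mmHg) | p = 10% | p = 20% | p = 30% |
|---|---|---|---|
| 0 | 5.0% | 5.0% | 5.0% |
| 2.0 | 5.7% | 6.2% | 6.6% |
| 2.8 | 6.4% | 7.5% | 8.2% |
| 4.45 | 8.5% | 11.2% | 13.1% |

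Simulation of the random-intercept REML model (2,000 trials per cell) agreed: 4.9-5.3% with no gap variation, 5.8-6.3% at 2.0 mmHg and 8.8-12.3% at 4.45 mmHg. The message effect in patients without microalbuminuria stayed at 4.4-7.0%, with no trend as τ² grew.

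**With baseline pressure adjusted.** Assume a patient-level pre/post correlation of 0.5 and a gap that is stable over time. The patient variance becomes 376.2 × (1 − 0.25) = 282.2. Since the covariate removes half of each practice's gap deviation, τ² becomes τ² × 0.25 = 0.99, 1.98 or 4.95.

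| Gap SD before adjustment (mmHg) | p = 10% | p = 20% | p = 30% |
|---|---|---|---|
| 2.0 | 5.2% | 5.4% | 5.5% |
| 2.8 | 5.5% | 5.8% | 6.1% |
| 4.45 | 6.1% | 7.0% | 7.7% |

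Simulation at p = 20% (3,000 runs) gave 5.0%, 6.3% and 7.8%. With a correlation of 0.4 the three values at p = 20% are 5.5%, 6.0% and 7.6%; with 0.6 they are 5.3%, 5.6% and 6.5%. If the gap is not stable over time, baseline adjustment removes less and the results move back towards the first table.

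**The case against.** The strongest reply is that the defect is read from silence. The random-effect sentence is generic and covers binary and continuous outcomes alike. The microalbuminuria analysis comes later in the section with no covariance structure of its own, and this is a condensed article whose analysis plan is not shown. That limits the point but does not remove it. The text states a model, and an analyst who follows it would fit a random intercept plus an interaction. A reader might infer that the protocol restricts the model to a single random effect; it does not say that, and a fuller plan may add the coefficient.

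A reader might also infer that the interval is certainly too narrow. The documents do not support this, because they give no variance for the gap, and at zero variance the test is correct. Nor should 11-13% be taken as the expected error. It needs a gap that varies as much as the whole planned between-practice SD, at 20-30% prevalence, and a model without the baseline covariate that the plan includes where appropriate.

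Finally, the primary blood-pressure outcomes are practice mean levels. The practice intercept covers that comparison, so nothing here counts against the overall message effect.

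The objection that random-coefficient models can be hard to fit is fair: in a small check many such fits failed to converge. At 10-20% prevalence each gap rests on only about 6-12 patients with microalbuminuria per practice. The alternative analysis therefore has to be fully specified.

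**Conclusion.** The point holds conditionally. As written, the differential effect is a cross-level interaction tested with a practice intercept alone, and its uncertainty is understated whenever the microalbuminuria gap varies between practices.

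For systolic pressure, under 10-30% prevalence and a gap SD of 2.0-4.45 mmHg, the nominal 5% test runs at about 5.7-13% without baseline pressure. With baseline adjusted it runs at about 5.2-8%, assuming a pre/post correlation of 0.5 and a stable gap. Prevalence, gap SD, correlation and stability are all assumptions. With the baseline covariate in place the likely error is modest. It concerns the differential effect only. This is an inexpensive improvement to an inference the plan sets out to make, and it does not threaten the primary blood-pressure result.

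**What to change.** In the systolic and diastolic models:

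1. Keep the pre-intervention blood pressure as a covariate.
2. Add a practice-level random coefficient for baseline microalbuminuria, correlated with the practice intercept.
3. Test the message-by-microalbuminuria term on practice-level degrees of freedom.
4. Prespecify the alternative in case that model cannot be fitted: estimate each practice's baseline-adjusted gap and compare the 34 gaps between arms with a t test (34 − 2 = 32 degrees of freedom). State in advance what counts as failure to fit, whether gaps are weighted, and how practices with few or no microalbuminuria patients are handled.

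In simulation an unadjusted t test of practice gaps held its error at 4.8-5.4%.

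The cost is a few sentences of analysis wording, one or two extra variance parameters, possible convergence trouble and a somewhat wider interval. At 20% prevalence the SE rises from 2.11 to 2.22-2.61 mmHg without baseline. With baseline adjusted it rises from √(4 × 28.4/34) = 1.83 to between √(4 × 29.4/34) = 1.86 and √(4 × 33.4/34) = 1.98 mmHg.

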### Interventions

The precise details of the intervention (wording and clinical content) were developed by a multi-disciplinary group, including representatives of primary care, secondary care, laboratory services, and the research team. The content of the messages is congruent with the local diabetes guideline and is evidence-based. The messages give succinct educational information regarding appropriate patient management (Table 1). The interventions were introduced in two phases, with Phase One demonstrating intervention feasibility and justifying continued funding for Phase Two.

**Table 1 T1:** Conditions and content of brief educational messages attached to test reports.

**Study phase**	**Type and attachment of message**	**Content of message**
Phase One	Unconditional; attached to all cholesterol reports	For type 2 diabetes &*age *≥ *40 yrs*: on simvastatin 40 mg? See [local guideline] for detail and exclusions
	Conditional; attached to all HbA1c reports	If HbA1c < 6.5%
		"Within target for type 2 diabetes"
		If HbA1c 6.5 – 7.0%
		"For type 2 diabetes, consider increasing oral therapy"
		If HbA1c 7.0–8.0%
		"If type 2 diabetes: on max oral therapy, *e.g*., Metformin 1G BD + gliclazide 160 mg BD?"
		If HbA1c > 8.0%
		"If type 2 diabetes, consider insulin if on max oral Rx, *e.g*., Metformin 1G BD + gliclazide 160 mg BD"
Phase Two	Unconditional; attached to all albumin: creatinine ratio (ACR) test reports	Newcastle Diabetes Guideline Footcare: all patients annual review of sensation, pulses, footwear education
	Conditional; attached to all ACR test reports	If ACR above 2.5
		If confirmed microalbuminuria: aim for BP < 130/80 in type 2 diabetes
		If ACR below 2.5
		If no microalbuminuria: aim for BP control < 140/80 in type 2 diabetes

Phase One messages are attached to electronic and paper test reports of HbA1c. From general practice, almost all requests for HbA1c will relate to patients with diabetes. The messages are of two types. The first message relates to glycaemic control, is conditional on the HbA1c level, and gives general advice about appropriate treatment. The second message (again on an HbA1c test result form) gives a non-specific message relating to the treatment of hypercholesterolaemia in patients with diabetes. This started in December 2005.

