Phase Two messages are attached to ACR test reports and are also of two types. The first message relates to foot inspection and is attached to all ACR test reports. The second message relates to blood pressure control, is conditional on the ACR level, and gives advice on target blood pressure (BP) levels for patients with and without a diagnosis of microalbuminuria. This started in October 2006.

The clinical foci of the interventions (*e.g*., glycaemic control) described here were selected because of their clinical importance. We also considered whether there would be scope for measurable improvements in patient outcomes and relevant outcome data available.

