### Outcomes

For Phase One, the two primary outcomes will be the general practice mean levels of HbA1c and cholesterol. We hypothesise that in practices receiving the glycaemic and cholesterol messages, compared to those practices not, the mean HbA1c and cholesterol values will be lower, respectively. Secondary outcomes for Phase One include the number of HbA1c and cholesterol tests requested (standardised for practice size) and the proportions of patients within each practice meeting QOF targets for glycaemic and cholesterol control.

For Phase Two, the primary outcomes will be the general practice mean levels of diastolic and systolic BP, and proportions of patients having undergone foot inspections. We hypothesize that in practices receiving the blood pressure messages compared to those practices not, the mean diastolic and systolic blood pressure values will be lower; and in those receiving foot inspections messages, the proportions of patients receiving a foot inspection will be higher. Secondary outcomes for Phase Two include: the proportions of patients in each general practice within target levels for blood pressure control according to the presence or otherwise of recorded microalbuminuria (which requires tighter BP control); the overall number of ACR tests requested (standardised for practice size); and the number of ACR tests requested (standardised for practice size) for patients with and without a diagnosis of microalbuminuria.

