### Practice-held data

General practices routinely collect standardised patient data that contribute to the calculation of QOF scores. Although 'exception reporting' allows practices to exclude patients with diabetes who consistently do not attend for care, practice data are scrutinised for completeness by local Primary Care Trusts (PCTs). These QOF data will be used to measure the primary outcomes for the trial,*i.e*., practice mean levels of HbA1c, cholesterol, diastolic and systolic BP, and proportions of patients having undergone foot inspections. Target levels for BP control depend on whether microalbuminuria is present. These data will also allow us to identify the subgroup of patients with a diagnosis of microalbuminuria so that their levels of BP control can be determined.

Collection and processing of these data will be undertaken on our behalf by Newcastle PCT, and all data will be anonymised before being transferred to the research team. Additional consent will be sought from practices for this data collection. To minimise the impact on practices, pre- and post-intervention outcome data will be collected during a single visit to individual practices. Data collection periods will cover 24 month pre-intervention periods (to provide baseline values), and up to 18 months post-intervention for phase one and eight months for phase two.

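### The split by baseline microalbuminuria groups patients with no ACR result with tested negatives, so the planned differential-effect contrast cannot be read cleanly as effect modification

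*Protocol article*

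**What the plan says.** **Message rule (Interventions, Table 1 and text).** The BP message is described as "Conditional; attached to all ACR test reports". Above an ACR of 2.5 it reads "If confirmed microalbuminuria: aim for BP < 130/80 in type 2 diabetes"; below 2.5 it reads "If no microalbuminuria: aim for BP control < 140/80 in type 2 diabetes". The accompanying text says that the message "is conditional on the ACR level, and gives advice on target blood pressure (BP) levels for patients with and without a diagnosis of microalbuminuria". A patient generates a message only by having an ACR test reported.

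**Grouping for outcomes (Outcomes; Practice-held data).** The secondary outcome on BP targets is split "according to the presence or otherwise of recorded microalbuminuria (which requires tighter BP control"). The source is practice-held data: "These data will also allow us to identify the subgroup of patients with a diagnosis of microalbuminuria".

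**Model (Statistical analysis).** The population is all registered patients with diabetes under practice or shared care, with no requirement for an ACR test. The plan then states "We will assess any change in blood pressure across all participants but fit a different effect for patients with microalbuminuria at baseline", and adds "This analysis will allow us to determine whether the messages had a differential effect according to whether microalbuminuria is present".

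**The concern.** The message rule and the analysis use different definitions. Under the message rule, the absence of microalbuminuria means a measured ACR below 2.5. In the analysis there is one separate term for recorded microalbuminuria within the whole diabetic population, which makes two groups. The second group holds patients tested and negative together with patients who have no ACR result.

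The patients without a result differ from the true negatives in two ways. Their status is unknown, and while they remain untested no report carrying the message is issued for them. Patients with recorded microalbuminuria can be expected to have had an ACR test at some point. The contrast between the groups may therefore mix microalbuminuria with exposure to the message. If the message worked equally well in everyone it reached, the comparison group could still show a smaller effect, and the plan would read this as effect modification.

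The BP-target outcome has a related weakness. Its target depends on microalbuminuria status, so patients of unknown status would be scored against the target for patients without it.

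**Working it through.** **Inputs from the protocol (Sample size; Practice-held data).** 34 practices, 62 patients per practice, ICC 0.05 for continuous outcomes, systolic SD 19.9 mmHg, 5% significance, 80% power, detectable systolic difference 4.98 mmHg, eight months of Phase Two follow-up. A two-sided test and 17 practices per arm are assumed.

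**Inputs not in the documents (assumed, with ranges).** The shares of patients with no ACR report in the eight months, and the prevalence of recorded microalbuminuria (10% to 30%, with 25% as the working value).

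**Step 1. Reproduce the plan's figure.**
- Design effect: 1 + (62 - 1) x 0.05 = 4.05.
- Effective number per arm: 17 x 62 / 4.05 = 260.2.
- Detectable effect: (1.960 + 0.842) x sqrt(2 / 260.2) = 0.246, which rounds to the stated 0.25.
- 0.25 x 19.9 = 4.98 mmHg, as stated.

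**Step 2. Spurious difference between groups.** Let the true effect be 4.98 mmHg in every patient reached, whatever the status, and zero in patients not reached. Let n be the share without an ACR report during follow-up in the group without recorded microalbuminuria, and m the same share in the group with it.
- Effect without: 4.98 x (1 - n). Effect with: 4.98 x (1 - m).
- Spurious difference: 4.98 x (n - m).

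For a given n this is largest at m = 0.

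**Step 3. Standard error of the contrast.** Both groups occur within practices, so the within-practice SD applies: 19.9 x sqrt(0.95) = 19.40. With 34 x 62 = 2,108 patients and prevalence p, SE = 19.40 x sqrt(4 / (2,108 x p x (1 - p))). This gives 2.82, 2.11, 1.95 and 1.84 mmHg at p = 10%, 20%, 25% and 30%.

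**Step 4. Chance of a significant contrast when the message works equally in both groups** (normal approximation, p = 25%, SE 1.95):

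| n - m | Spurious difference (mmHg) | Chance of p < 0.05 |
|---|---|---|
| 0 | 0 | 5.0% |
| 7% | 0.35 | 5.4% |
| 10% | 0.50 | 5.8% |
| 20% | 1.00 | 8.0% |
| 30% | 1.49 | 11.9% |
| 40% | 1.99 | 17.5% |

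At n - m = 40% the last column runs from 10.9% (p = 10%) to 19.1% (p = 30%). Simulation of 34 practices of 62 patients at p = 25% and m = 0 (1,500 runs) agrees: 17.8% at n = 40%. The 7% row corresponds, for example, to n = 40% and m = 33%.

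**Step 5. Cost of leaving the untested out of the contrast.** At p = 25% there are 527 patients with recorded microalbuminuria and 1,581 without. If a share u of the 1,581 has no ACR result, SE = 19.40 x sqrt(4/527 + 4/(1,581 x (1 - u))). This is 1.98, 2.01, 2.05 and 2.11 mmHg for u = 10%, 20%, 30% and 40%, against 1.95 with all patients.

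**The case against.** Five points deserve an answer.

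- **The grouping of untested patients is inferred.** The protocol never says outright that a patient without an ACR result counts as negative, and a full analysis plan might settle it. This limits the certainty. Even so, one separate term within all participants, and a split into presence or otherwise of a record, leave no third group. The protocol also commits to what this model will determine.
- **A reader might infer that the message cannot reach untested patients.** The documents do not support that. A patient untested at baseline may be tested in the eight months. The messages are reminders to clinicians, and the Background cites reminders on X-ray reports that reduced later X-ray requests, a change not confined to patients who already had a report. Zero effect in the untested is an assumption.
- **Past testing is not exposure.** A patient with recorded microalbuminuria who is not retested in the eight months generates no message either. This stands. It is why the size depends on n - m, and why the rates of about 12% and 18% at 30% and 40% apply only when every recorded-positive patient is retested.
- **A reader might infer that the treatment estimates are biased.** They are not. Practices are randomised and status is taken at baseline, so each within-group arm comparison remains a valid intention-to-treat estimate. Only the interpretation of the difference between groups is affected.
- **Three baseline groups do not equalise retesting during follow-up.** This is also true. The change removes the unknown-status patients from the contrast but leaves any difference in retesting between the two remaining groups.

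**Conclusion.** The concern holds as a limit on interpretation. As written, the two-way split places patients of unknown status, who are less likely to generate an ACR report, among the true negatives. The difference between groups therefore cannot by itself show that the message's effect depends on microalbuminuria, which is what the plan says it will determine. The main BP comparison is unaffected.

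The size cannot be fixed from the documents. If the message acts only through a patient's own report and the true effect is 4.98 mmHg, the spurious difference is about 4.98 x (n - m) mmHg. It is negligible when the two groups are tested at similar rates. At the upper end (m = 0) it is 0.5 to 2.0 mmHg for n from 10% to 40%, with a false-positive rate of up to about 18% at an assumed 25% prevalence. Any effect of the message on the care of untested patients would shrink these figures.

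A second mismatch points the same way. One ACR above 2.5 triggers wording for confirmed microalbuminuria, while the analysis uses a recorded diagnosis. A tested patient above 2.5 with no recorded diagnosis would fall in the comparison group.

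**What to change.** From the 24-month pre-intervention records, classify each patient at the start of Phase Two as (1) recorded microalbuminuria, (2) ACR-tested without microalbuminuria, or (3) no ACR result. Then:

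- base the differential-effect contrast on groups 1 and 2;
- give group 3 its own term, so that all patients stay in the overall BP analysis;
- report the BP-target proportion for group 3 separately;
- reconcile the ACR 2.5 message rule in Table 1 with the recorded-diagnosis definition in Outcomes and Practice-held data, and state how a tested patient above 2.5 without a recorded diagnosis is classed for analysis;
- note, when interpreting the contrast, that retesting during follow-up may still differ between groups 1 and 2.

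The cost is one extra model category and a flag for any baseline ACR result. ACR test counts by diagnosis status are already a secondary outcome, and baseline and follow-up data are to be collected in a single visit per practice. The contrast loses a little precision: at 25% prevalence its SE rises from 1.95 to about 2.05 mmHg if 30% of those without a record are untested, and to 2.11 mmHg if 40% are.
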